**Fig. 2 Fig2:**
[figure not shown]
Study flow

### Patient participants

Patient eligibility criteria include (1) 50–80 years old on the upcoming appointment date; (2) currently smoking cigarettes or quit within the past 15 years; 3) a ≥ 20 pack-year smoking history; (4) non-adherent to lung screening (never screened or > 13 months since last screen); (5) English-speaking; (6) scheduled for a clinic appointment during the upcoming 3–8 weeks; (7) able and willing to provide meaningful consent; and (8) able to complete the phone-based interviews and intervention. Individuals with a prior diagnosis of lung cancer documented in the EHR will be excluded.

### Study procedures

All study procedures were reviewed and approved by the Georgetown-MedStar Institutional Review Board.

### Clinic recruitment and procedures

We have formed partnerships with primary care leadership and providers who facilitated introductions to the 4 clinical practice sites. To introduce the study, we met with practice leadership (e.g., Medical Directors, Division Chiefs) to review the study requirements. Following the introductory meetings, we received buy-in from MedStar primary care leadership (e.g., Assistant Vice President/Vice Presidents of Primary Care Services). Prior to the study start, clinics were sent a Letter of Agreement. Our team introduced the study and provided education about lung screening during an existing practice meeting. We also provided clinics on the best practices for assessing tobacco use and connecting patients with smoking cessation treatment. For the Multilevel Clinics, we notified the providers of the new clinician reminder and provided information on patient selection, when to expect the prompts and how to use them, and details about the patient component. The Comparison Clinics will identify and refer screen-eligible patients utilizing usual care as described below.

### Patient recruitment and procedures

During the recruitment period, the research assistants will access the list of potentially eligible individuals from an EHR report that our team developed to identify patients with an upcoming visit who are 50–80 years old with an ever-smoking history. Due to the limitations of the EHR smoking history data, including a large number of missing data for the pack-years field (90% on average are missing pack-years), we are conservatively estimating 25% of those reached will be eligible for the study (Fig. 2). The report utilizes EHR appointment and clinical data and will be imported into the study’s REDCap database weekly by the study team. Our team will invite patients to participate in the study through a mailed invitation letter, email, and the myMedStar patient portal, followed by phone calls (up to 3 attempts). During this call, the research staff member will describe the study, determine eligibility, obtain verbal consent, and complete the baseline assessment. We expect to enroll *n* = 184 in the Multilevel Clinics and *n* = 184 in the Comparison Clinics (total *N* = 368).

Following baseline (T0), Multilevel Clinic participants will receive the phone-based inreach and education within 1 week to 3 days prior to the visit. The comparison clinics will not receive the bundled strategies, but eligible participants will be enrolled and followed to measure the outcomes. All patient participants will receive up to $50 in total for their participation.

### Provider recruitment and procedures

In the pre-implementation phase, we will conduct semi-structured interviews to understand the contextual factors related to the feasibility and acceptability of the strategies with MedStar primary care leadership, primary care providers, RN practice managers, and medical office assistants (*n* = 25). We will conduct 30-min individual interviews which will be recorded and transcribed. During the implementation phase, the study team will send the EHR message to the primary care providers in the Multilevel Clinics 2 business days before the screening-eligible patient's scheduled visit. The messages will notify providers of the patient’s eligibility and encourage discussion of the benefits and limitations of screening. Post-implementation, we will conduct semi-structured interviews with the same participants from the pre-implementation phase. All provider participants will receive up to $100 in total for their participation.

### Multilevel implementation strategies development

Reported elsewhere [44], we completed developmental phases to finalize the content of the provider-level prompt and the patient-level inreach and education component. These phases were iterative in nature and included an online survey of *n* = 22 MedStar primary care providers, usability testing (*n* = 7), clinic shadowing to understand provider workflow, and partnering with a MedStar primary care clinic (Mitchellville, MD) for a 6-month period to optimize and refine the provider prompt. Similarly, we used a multi-step process for the patient-level component to adapt two existing, evidence-based tools: the ShouldIScreen decision aid [45] and the T.A.L.K. Back! model [46] to promote patient activation. We received feedback on the patient education component and the participant-facing materials from a Patient Advisory Board and conducted pilot testing with screen-eligible patients (*n* = 23) to refine the strategy described below.

### Patient-level inreach and education

The patient-level component includes receiving the educational booklet and a 20-min phone-based inreach session from a trained specialist approximately 1 week before the scheduled clinic visit. The information in the booklet and phone script covers the risk of developing lung cancer, along with how participants manage this risk by engaging in lung screening and smoking cessation. Additionally, it addresses self-efficacy by providing information on the lung cancer screening process. The provided resources cover possible barriers to screening (e.g., stigma from smoking, medical mistrust) and emphasize the importance of shared decision-making and discussing screening with their provider using an adapted T.A.L.K. Back! model. The session also targets patient activation by teaching good communication skills and empowering patients to feel ready to talk with their provider about lung screening.

### Provider-level reminder

We will send the clinician reminder (Fig. 3) 2 days before the screening-eligible patient’s clinic visit to primary care providers from the Multilevel Clinics. The study team will build a web-hosted application to automatically pull data from an Application Programming Interface (API) to copy the baseline (T0) smoking history from the study database into a patient-specific prompt template. This prompt will be delivered through the EHR’s Message Center with a subject line, “Consider Lung Screen CT – [Patient Name]”. Based on the pilot work, the content in the body of the message includes a tabular presentation of the patient’s smoking history (e.g., age, smoking status, pack-years, age started); 2021 USPSTF recommendation; information about insurance coverage; discussion points to engage in shared decision making (including an auto-text shortcut for providers to document shared decision-making); and ordering and billing information. A set of talking points (discussion of the benefits and harms of screening, adherence to annual screening, and smoking cessation) is attached to the message. For patients currently smoking, the document includes instructions to access the order for e-referral to the tobacco quitline, the orderset of the six FDA-approved cessation medications, and prompts to encourage quitting.

**Fig. 3 Fig3:**
[figure not shown]
Visual of message

### Usual care

At the time of designing this study, lung screening was not included in the list of health recommendations like other preventive services (e.g., breast cancer screening, colorectal cancer screening) in the EHR to prompt providers. Providers had to utilize the smoking history data included in the record to identify patients eligible for lung screening. However, the total pack-years field in the EHR had a large amount of missingness (90% on average are missing pack-years) across the 4 practice sites, possibly due to the field lacking automation. Usual care in MedStar primary care is expected to change as a result of ongoing related work led by our team. New forms are being released to improve the assessment of tobacco use, including automated calculation of pack-years, and to facilitate smoking cessation and lung screening referrals by displaying in the recommendations tab for eligible patients.

### Measures

We will use mixed-methods and multilevel assessments (Table 1). At the *patient-level*, participants will be assessed at baseline and 1-week post-visit to measure the primary outcomes: provider-patient discussion (“Did you have a discussion with your doctor about lung screening?”), screening intentions (“Do you plan to have a CT scan to check for lung cancer in the next 6 months?”), and knowledge using 11 true/false items from the literature [47]. We will administer the Questionnaire on the Quality of Physician–Patient Interaction scale to measure patient-reported provider-patient communication [48]. The Lung Screening Health Beliefs Scale will measure perceived risk, self-efficacy, benefits, and barriers [49]. The Consumer Health Activation Index will be administered to measure patient activation [35]. We will evaluate potential moderators including race (non-Hispanic African American vs. non-Hispanic White vs. other), smoking status (current vs. former), and health literacy (“How often do you find numbers, figures, or graphs to be useful in making a health-related decision?”) [50].

**Table 1 Tab1:** Complete measures

		**T0**	**T1**	**T2**
		**Baseline**	**1 week**	**6 months**
***Patient-level variables***	*Primary outcomes*: Provider-patient discussion, lung screening intentions, screening knowledge	**X**	**X**	
	*Secondary outcomes*: Lung screening referrals, completion rates (EHR)	**X**		**X**
	*Moderators*: Race, smoking status, health literacy	**X**		
	*Intervention targets*: Physician–patient communication, perceived risk, self-efficacy, benefits/barriers, patient activation, attended visit/visit type	**X**	**X**	
	*Covariates*: Demographics, social determinants of health, tobacco behaviors, cancer screening history, psychological variables (e.g., stigma, medical mistrust)	**X**		
***Provider-level variables***	Demographics	**X**		
	Lung screening practices	**X**		**X**
	Lung screening attitudes	**X**		**X**
	Intervention acceptability, usability, intervention, effectiveness			**X**
***Implementation variables***	Reach: % of patients offered trial enrollment and the % enrolled out of the number of eligible patients who had a visit during the recruitment period	**Pre-post implementation**		
	Effectiveness: screening referrals and screening completion rates			
	Adoption: % of messages opened by the receiving provider; fidelity of the patient component			
	Implementation: feasibility, acceptability			

At the *provider-level*, we will assess provider demographics (age, race and ethnicity, years in practice, academic appointment), checklist of the current lung screening process, and attitudes toward lung screening using semi-structured interviews pre-post trial. We will use items from the validated Technology Acceptance Model to measure the usability and effectiveness of a technology-oriented strategy [51].

Secondary outcomes, screening referrals, and screening completion rates will be extracted from the EHR database at 6-month post clinic enrollment. To measure temporal trends at the *clinic-level,* lung screening orders and completion rates will also be collected 12-month pre- and post-study. Additionally, in pre-implementation, we conducted semi-structured interviews with the Medical Directors and Operations Managers for contextual purposes. We asked questions about current practice volume, standard rooming practice, workflow for reviewing and addressing health recommendations for lung cancer screening and other preventive services, and information on screening referrals and follow-up.

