Clinician reminders are one of the Expert Recommendations for Implementing Change (ERIC) discrete implementation strategies that prompt clinicians to recall information or use a clinical innovation, like evidence-based screening recommendations. In general practice, provider prompts and best practice alerts have been effective in promoting evidence-based and guideline-concordant care. However, providers have reported “alert fatigue” suggesting that reminders are ignored [36–38]. To date, three studies have been conducted to evaluate the impact of clinician reminders on lung screening referrals and have found these to be effective approaches to improving lung cancer screening in primary care [24, 39, 40]. A pre-visit planning message is a type of clinician reminder that aims to help the provider conduct the clinic visit more effectively by gathering information ahead of time so they can devote more attention during the visit to discussing that information and responding to the patient’s questions. An advantage of this type of reminder is that it is not disruptive to the provider’s workflow like pop-up alerts may be. This type of clinician reminder may be especially important for lung cancer screening, because to be eligible for coverage, the Centers for Medicare & Medicaid Services guidelines require a shared decision-making visit [41]. This visit is required to be conducted by a healthcare provider with the patient prior to the first screening referral to discuss the benefits, risks, and limitations of screening, and smoking cessation. To address provider time constraints about lung screening, this study will send a pre-visit planning message as a reminder to discuss screening with eligible patients.

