### Statistical analysis plan

We will examine the distributions of all variables to describe the characteristics of the study population. We will conduct analyses using *t*-tests, *χ*^2^ tests, and Pearson or Spearman correlation coefficients to assess the bivariate associations between the baseline characteristics and the outcome variables. Bivariate analyses will also be conducted to assess the associations between the study arm and baseline characteristics. Owing to any significant differences detected at the 0.05 level, the variables associated with both the study arm and the outcome of interest will be entered as covariates in subsequent analyses. To test the overall difference between the study arms on the primary outcomes, we will conduct logistic regression models (for provider-patient discussion — yes/no, screening intentions — likely/unlikely) and a linear regression model (for the screening knowledge score). Logistic regression analyses will also be conducted on the secondary screening outcomes (lung screening referral — yes/no, lung screening completion — yes/no). This study will explore potential moderators (e.g., race, health literacy, smoking status). That will be done by evaluating the presence of interactions between the moderators and study arm, one at a time, after adding them to the regression models described above. In sensitivity analyses, we will evaluate the robustness of our findings by using versions of the above models with generalized estimating equations (GEE). These models will use the sites as clusters, and assume an exchangeable working correlation structure.

For the qualitative analysis, we will use a deductive thematic analysis based on a priori PRISM constructs, with additional codes added as needed. Initial codes will be generated by two coders and each of the coders will review two transcripts for each sub-population (i.e., patient and provider) to reach a consensus on the coding framework and application of codes prior to splitting up the remaining transcripts.

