This study will provide preliminary data on the effectiveness and feasibility of multilevel implementation strategies to improve lung screening utilization in an equitable manner. Future work will include a large 2 × 2 factorial, cluster randomized trial to compare the independent and overlapping contributions of the provider and patient implementation strategies. Study limitations include the quasi-experimental study design, which will limit the ability to determine causality. Second, we considered recruiting all potentially eligible patients irrespective of having an upcoming appointment, as those with a scheduled appointment may be sicker and/or more engaged in their healthcare. However, a primary endpoint is whether the provider-level prompt and the patient-level activation impact the discussion about lung screening at the clinical encounter, and so we elected to include an upcoming appointment as an eligibility criterion. It is well documented that the collection of smoking-related data (e.g., smoking duration, cigarettes per day, pack-years) in the EHR is not standardized and is often incomplete. The proposed study will use the EHR data to identify potentially eligible individuals based on age (50–80 years old) and smoking status (current and former). However, there will be a high number of screen failures as well as patients who may be eligible for lung screening but are not approached for the study due to data missingness. In other ongoing work, our research team is conducting a quality improvement project to improve how tobacco use is assessed and documented in the primary care setting across MedStar.

Following the successful completion of this study, future work will include partnering with an expanded number of primary care practices and utilizing a cluster randomized controlled trial to determine if these implementation approaches facilitate an increase in lung screening rates equitably.

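### The primary discussion item, as printed, is not tied to the study visit, and the covariate rule does not guarantee adjustment for discussions reported at baseline

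*Protocol article*

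**What the plan says.** **Item and timing.** Under Measures, the discussion outcome is given as the single question "Did you have a discussion with your doctor about lung screening". The intention item in the same sentence does carry a time frame: "Do you plan to have a CT scan to check for lung cancer in the next 6 months". On timing, the section says "participants will be assessed at baseline and 1-week post-visit to measure the primary outcomes", and Table 1 marks the discussion outcome at T0 and T1.

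**Intended meaning.** The limitations paragraph of the Discussion says a primary endpoint is whether the prompt and patient activation "impact the discussion about lung screening at the clinical encounter". That is a visit-specific event.

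**Population.** Patient participants must be "non-adherent to lung screening". This covers people never screened and people with more than 13 "months since last screen". On Medicare coverage, the Background says of the shared decision-making visit: "This visit is required to be conducted by a healthcare provider with the patient prior to the first screening referral".

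**Analysis.** Discussion (yes/no) is modelled by logistic regression on study arm. Covariates are chosen by bivariate testing at the 0.05 level: "the variables associated with both the study arm and the outcome of interest will be entered as covariates in subsequent analyses". No rule is stated for a participant who already answered yes at T0.

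**Power.** The article states 83% power for a 12-point difference in discussion at a significance level of 0.05, with 184 enrolled per arm. It does not state the comparison-arm rate, the number evaluable or the sidedness.

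**The concern.** The endpoint is meant to be an event at one visit, but the printed question does not say so. At T0 the study visit has not yet taken place, so a yes there can only refer to an earlier discussion. If the same words are used at T1, nothing in them excludes that earlier discussion.

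Earlier discussions are plausible. Previously screened patients whose last scan is old enough are eligible, and the article describes a provider discussion as a coverage condition for a first referral. A never-screened patient may also have discussed screening and not proceeded.

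Two consequences follow, depending on how prior discussion is distributed:

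- **Balanced between arms.** Both rates rise and the absolute difference shrinks. The T0 answer is then unlikely to be associated with arm, so the covariate rule leaves it out.
- **Unequal between arms.** Allocation is by clinic, with four clinics and no randomisation, so this is a real possibility. The carried-over answers would add to or subtract from the effect. The rule may pick this up, but only if the imbalance reaches significance.

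**Working it through.** **1. Reproducing the stated power.** The 83% cannot be rebuilt from stated inputs alone, but it can be reached. I used a two-sided 0.05 test (assumed), 1:1 allocation, pooled variance under the null, and no allowance for clustering:

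power = Φ{ [ |p2 − p1| − 1.96·√(2·p̄(1−p̄)/n) ] / √( [p1(1−p1) + p2(1−p2)]/n ) }

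- The knowledge figure (effect size 0.33, 83% power) implies n = 2·(1.96 + 0.954)²/0.33² ≈ 156 per arm. Since 156/0.85 ≈ 184, this matches enrolment with 15% attrition (assumed).
- With n = 156 and 10% vs 22%, power = Φ[(0.12 − 1.96·0.0415)/0.0410] ≈ 82.7%.
- With n = 184 and 13.6% vs 25.6%, power ≈ 82.9%.

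The stated power is therefore attainable. At these sample sizes it implies a low comparison-arm rate, about 10% to 14%.

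**2. Balanced carry-over.** Assume a share q of each arm had an earlier discussion, independent of what happens at the study visit, and that all of them answer yes at T1. The observed rate becomes q + (1 − q)·p, and the difference becomes (1 − q)·12 points.

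| q | Rates (true 10% vs 22%) | Difference | Power, n = 156, 10% vs 22% | Power, n = 184, 13.6% vs 25.6% |
|---|---|---|---|---|
| 0% | 10.0% vs 22.0% | 12.0 | 83% | 83% |
| 5% | 14.5% vs 25.9% | 11.4 | 71% | 73% |
| 10% | 19.0% vs 29.8% | 10.8 | 60% | 64% |
| 20% | 28.0% vs 37.6% | 9.6 | 44% | 48% |
| 30% | 37.0% vs 45.4% | 8.4 | 32% | 37% |

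Example at q = 10%, n = 156: Φ[(0.108 − 1.96·0.0486)/0.0482] ≈ 60%.

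**3. Unequal carry-over.** Take no true effect, a 10% visit-discussion rate in both arms, and q of 10% in one arm and 20% in the other. The observed rates are 0.10 + 0.90·0.10 = 19% and 0.20 + 0.80·0.10 = 28%. That is a spurious 9-point difference, and its direction depends only on which arm has more prior discussion.

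**4. What using the T0 answer recovers.** Under the model in step 2, everyone with a yes at T0 also says yes at T1, so that group carries no information on arm. The comparison rests on the T0-no group, with n·(1 − q) per arm and the full 12 points. With n = 156 and 10% vs 22%:

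- q = 10%: about 140 per arm, power about 79% (60% unadjusted).
- q = 20%: about 125 per arm, power about 74% (44% unadjusted).

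The T0 answer recovers most of the loss but not all of it. Anchoring the T1 item avoids the loss altogether.

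**The case against.** The strongest reply is that the timing supplies the missing reference. T1 is an interview one week after the visit, Table 1 also records visit attendance and physician–patient communication, and the item is in the simple past rather than asking whether a discussion ever took place. Many respondents would take it to mean that visit. The article may also condense the script, and a timepoint-specific lead-in could exist. This stands to the extent that carry-over is a risk created by the printed wording and not a documented fact. A reader might infer that the endpoint measures whether screening was ever discussed; the documents do not support that.

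Second, the share with a prior discussion is unknown. The article cites overall screening uptake of 3% to 20%, and patients up to date with screening are excluded, so the previously screened group need not be large. The coverage rule does not prove that every earlier scan followed a discussion the patient remembers. This also stands: 10% and 20% are illustrations.

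Third, the rates behind the 12 points are not given and may already refer to the item as worded. A reader might infer that the stated 83% is wrong, or that the trial has lost power. Neither is shown.

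Fourth, T0 discussion and cancer screening history are both collected, and the covariate rule can admit a significant imbalance. That offers partial protection against bias. It does nothing for balanced prior discussion, and an imbalance that matters can miss significance.

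**Conclusion.** The point holds as a mismatch between a primary endpoint's stated meaning and its printed wording, combined with a covariate rule that does not reliably repair it. Both elements are stated in the article, so this does not depend on what a separate analysis plan might add.

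The direction of the effect is not fixed. Balanced prior discussion dilutes the difference; unequal prior discussion across the four clinics can bias it either way. The size is conditional. With 156 evaluable per arm and 10% vs 22%, power goes from about 83% to about 60% at 10% carry-over and 44% at 20%. Those figures assume the comparison rate, the evaluable number, a two-sided test, full carry-over of earlier discussions independent of the visit, and no clustering. They show that a modest share would matter, not that such a share exists. The change is worth making because it is cheap and protects a primary outcome.

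**What to change.** - **T1 item.** Ask whether the participant and doctor discussed lung screening at the study visit, naming its date. Keep the open wording at T0 as a measure of any earlier discussion.
- **Primary model.** Enter the T0 discussion answer as a prespecified covariate in the logistic regression for discussion, whatever the bivariate screen shows.
- **Sensitivity analysis.** Repeat the arm comparison among participants who answered no at T0. If nearly all T0-yes participants also say yes at T1, the T0 coefficient may not be estimable, and this analysis becomes the clearer one.

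The cost is one line in the T1 phone script and one model term. Appointment data are already imported into the study database and the T0 answer is already collected. The small downside is that, if collection has started, responses taken under the open wording must be flagged; for those, the T0-adjusted and T0-no analyses still need no new data.
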